## **Discussion**

Previously, a meta-analysis on single vs low-profile double plating demonstrated that low-profile double plating attains the same healing rates as single plating without a higher chance of fracture-related infections. [7] This study however, was based on studies with relatively small sample sizes. The present NE study will provide the required evidence to confirm or revoke the aforementioned conclusions based on a more extensive study population.

191 Additionally, this study will form the basis for a more prominent use of the NE design in the surgical  
192 research. Due to its design, this study has a high feasibility with minimal burden to the participants,  
193 since the received care is that of daily clinical practice. Not only will the study help us understand if  
194 low-profile double plating has significant clinical and cost-effective benefits over single plating tech-  
195 niques in midshaft clavicle fractures, but it also provides new insights into how the NE design func-  
196 tions in a research field where it has rarely been used before.

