## Table 2. Outcome measures and planning

### Sample size calculation

The sample size calculation is based on the primary outcome (re-intervention). Based on a recent meta-analysis of our study group, a risk reduction of 10% is expected in favor of low-profile double plating compared to single plating. To demonstrate this difference using a chi-square-test ( $\alpha =$

0.05, power = 0.8) approximately 152 patients per treatment group are needed. To compensate for a potential 5% loss to follow-up, a total of 336 patients are required.

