## **Statistical analysis.**

The statistical package IBM SPSS Statistics for Windows, version 28.0, will be used for analysis. Depending on the normality distribution, baseline characteristics will be described as means and standard deviations or median and interquartile range for continuous variables. Categorical variables will be reported in counts and percentages. Differences between treatment groups will be analyzed with an independent samples student's T-test or Mann-Whitney-U test (depending on distribution). Categorical variables will be analyzed using the Chi-square test.

The primary outcome will be analyzed using logistic regression with revision surgery as the dependent and treatment as the independent variable. The relative risk (RR) will be calculated with a 95% confidence interval (95% CI). Multivariable logistics regression analysis will also be performed to account for potential known confounders including age and fracture type.

Missing data (caused by incomplete hospital documentation or loss-to-follow-up) will be addressed using multiple imputation techniques.

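### The Discussion promises to confirm equal healing and no excess infection, but the protocol states only a test of difference, sizes only for re-intervention, and gives no margin by which sameness could be judged

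*Protocol*

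**What the plan says.** The protocol's Discussion summarises the earlier meta-analysis as showing that "low-profile double plating attains the same healing rates as single plating without a higher chance of fracture-related infections". It notes that the underlying studies were small and then states: "The present NE study will provide the required evidence to confirm or revoke the aforementioned conclusions". The Background part of the Abstract gives the same two conclusions, and the same limitation, as the reason the study was designed.

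The Sample size calculation section uses re-intervention alone. There, "a risk reduction of 10% is expected in favor of low-profile double plating compared to single plating", with alpha 0.05, power 0.8 and about 152 patients per group. The section continues: "To compensate for a potential 5% loss to follow-up, a total of 336 patients are required".

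The Statistical analysis section plans t-tests or Mann-Whitney tests for continuous variables. For the rest it says: "Categorical variables will be analyzed using the Chi-square test". Logistic regression and a relative risk with a 95% confidence interval are given for the primary outcome. Non-union and fracture-related infection are secondary outcomes (Study outcomes; Table 1). The protocol states no non-inferiority or equivalence hypothesis, margin or expected rate for either.

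**The concern.** A test of difference can give evidence that two rates differ. Failing to reject does not show that they are alike, least of all when events are few. Confirming equal healing, or no excess of infection, requires an interval that excludes differences large enough to matter, and so a statement of how large that is. The protocol makes the promise without either element.

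At stake is what may be said about the safety of the newer technique. The re-intervention comparison is a superiority question and is unaffected. For healing and infection, the text promises a conclusion that its stated analysis cannot deliver, and these are the conclusions that the Abstract gives as the reason for the study.

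**Working it through.** **The plan's own figure.** The 152 per group cannot be derived from the stated inputs, because no re-intervention rate is given for the sizing. Read as an absolute 10-point reduction with a two-sided test, it fits rates near 16% v 6% (153 per group). This concerns re-intervention only; nothing in the calculation refers to non-union or infection.

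**Inputs for the check.**
- Evaluable patients: 336 × 0.95 / 2 = 159.6, taken as *n* = 160 per arm (total and loss from Sample size calculation).
- Equal arms and no allowance for clustering by centre: assumptions.
- Event rates of 1%, 2%, 3% and 5%: assumptions, since the protocol gives none.
- Two-sided alpha 0.05 for the chi-square test (sidedness is not stated) and one-sided 0.025 for non-inferiority: assumptions.

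**Power of the chi-square test to detect a doubling.** With p̄ the mean of the two rates,

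power = Φ{[|p1 − p2| − 1.96·√(2p̄(1 − p̄)/n)] / √([p1(1 − p1) + p2(1 − p2)]/n)}.

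For 2% v 4%: Φ[(0.02 − 1.96 × 0.01907) / 0.01904] = Φ(−0.913) = 0.18.

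| True rates | Power, normal approximation | Power, exact |
|---|---|---|
| 1% v 2% | 11% | 10% |
| 2% v 4% | 18% | 17% |
| 3% v 6% | 25% | 25% |
| 5% v 10% | 40% | 39% |

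Over this range a true doubling would give p > 0.05 about 60% to 90% of the time. With 152 per arm, power is up to 2 points lower.

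**Precision and non-inferiority power when the true rates are equal.** Half-width = 1.96·√(2p(1 − p)/n). At 2% this is 1.96·√(2 × 0.02 × 0.98/160) = 3.1 points, with 0.02 × 160 = 3.2 events expected per arm. Non-inferiority power = Φ(margin/SE − 1.96), with SE = √(2p(1 − p)/n). At 2% and a 5-point margin this is Φ(0.05/0.01565 − 1.96) = Φ(1.23) = 0.89. The margins are illustrations, not proposals.

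| Rate in both arms | 95% CI half-width (points) | Power, 3-point margin | Power, 5-point margin |
|---|---|---|---|
| 1% | 2.2 | 77% | 99% |
| 2% | 3.1 | 48% | 89% |
| 3% | 3.7 | 35% | 75% |
| 5% | 4.8 | 23% | 54% |

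These are normal approximations and are rough with so few events.

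**Higher rates.** Power for a doubling is about 53% at 7% v 14%, 60% at 8% v 16% and 71% at 10% v 20%. The statement that a doubling would usually be missed therefore holds only below roughly 7%.

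**The case against.** There is a fair case on the other side.

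- The stated aim is to compare, healing and infection are secondary, and no non-inferiority objective is declared, so no declared hypothesis is mis-tested. That stands. The point concerns a promise in the text and leaves the primary analysis alone.
- The sentence allows for revoking as well as confirming, and a test of difference can bear on the former. That also stands, but only for half of the promise.
- The chi-square sentence closes a paragraph that opens with baseline characteristics, so applying it to secondary outcomes is an inference. If it covers baseline only, the protocol names no analysis for these outcomes, and the promise has less support still.
- Margins and interval methods for secondary outcomes are often left to the SAP, which is not shown. Their absence alone is therefore no fault. The unconditional promise, and the sizing on another endpoint, are in the protocol and can be corrected there.

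A reader might go further and infer that the sample is too small to support any non-inferiority statement. The documents do not support that. Adequacy depends on a margin and rates they do not give: 160 per arm would do well for 5 points at a rate of 2% or less, and poorly for 3 points at the same 2%. Nor can low rates be assumed with confidence for non-union, since Table 1 counts asymptomatic as well as symptomatic cases.

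A reader might also infer that p > 0.05 will be reported as proof of safety. The protocol contains no such rule of interpretation. It is a risk that the wording leaves open, not something the plan states.

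**Conclusion.** The point holds in limited form. The Discussion claims a property, the ability to confirm equal healing and no excess infection, that the stated test, sizing and absence of a margin do not provide. If event rates are 1% to 5%, with 160 evaluable per arm, equal arms and no clustering, a non-significant chi-square result would be weak evidence: power for a doubling is about 10% to 40%, and the interval extends about 2 to 5 points either side of the estimate. Above roughly 7% the power argument weakens, but a test of difference still cannot establish sameness. The correction should be made; it does not touch the primary outcome, the sample size or data collection.

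**What to change.** In Statistical analysis, state that non-union and fracture-related infection will each be reported as a risk difference (double minus single plating) with a score-type 95% confidence interval, not as a chi-square p-value alone.

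In the Discussion, say that the study will estimate these differences and that a non-significant test will not be taken as confirming equality. Reserve wording such as 'same' or 'not higher' for the case where the upper confidence limit lies below a margin that was justified and fixed before any data are seen. That margin may sit in the SAP. If none is set, the text should promise estimation only.

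The cost is a few lines of wording and one results table, with no extra patients. The downside is a weaker stated claim.

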## 198 **List of abbreviations**

|     |      |                                             |
|-----|------|---------------------------------------------|
| 199 | AE   | Adverse Event                               |
| 200 | BMI  | Body MASS Index                             |
| 201 | CI   | Confidence Interval                         |
| 202 | DASH | Disabilities of the arm, shoulder, and hand |
| 203 | EQ   | EuroQol                                     |
| 204 | NE   | Natural Experiment                          |
| 205 | OR   | Odds Ratio                                  |
| 206 | RCT  | Randomized Controlled Trial                 |

## 208 **Ethics approval and consent to participate**

209 This study was ethically approved by the Northwestern and central Swiss ethics commission. The  
210 identifier number is 2022-00574

## 212 **Publication**

213 Publications based on the results obtained shall not be made before the first multicentre publication  
214 or presentation, which shall be coordinated by the principal investigator unless otherwise agreed in  
215 writing. The manuscript shall be published in a peer-reviewed journal.

216

#### 217 **Consent for publication**

218 Not applicable

219

#### 220 **Availability of data and materials**

221 The datasets used and/or analyzed during the current study are available from the corresponding au-  
222 thor upon reasonable request.

223

#### 233 **Acknowledgments**

234 Not applicable

235

## 236 Protocol Amendments

237 Relevant protocol changes (eg changes to eligibility criteria, outcomes, analyses) will be discussed  
238 within the research group and have to be approved by the trial registries, the Northwestern and cen-  
239 tral Swiss ethics commission and the sponsor.

240

